### Statistical analysis

Statistical analyses will be performed using SPSS 25.0 (IBM SPSS Statistics, Armonk, NY). An intention-to-treat (ITT) approach will be used to analyse the data. All data will be checked for normal distribution using the Kolmogorov test. For normally distributed data, continuous variables will be analysed using the independent Student’s *t* test, and the variables will be presented as the mean ± standard deviation (SD). Nonnormally distributed data will be compared using the Mann‒Whitney *U* test where appropriate, and data will be presented as the median and interquartile range (IQR). For categorical variables, cross-tabulation and the Pearson chi-squared test will be applied, and variables will be categorized as numbers and/or percentages of the total. A logistic regression model will be applied to detect any potential confounding factors. To compare the continuous measurements of HR and NIBP between the groups, the area under the curve (AUC) for each value will be calculated over the different measurement time points during the procedure. To compare the continuous measurements of HR and NIBP between the groups, the area under the curve (AUC) for each value will be calculated over the different measurement time points during the procedure. Missing data are neglected or multiple imputation will be used when > 40% and identified as missing, not at random. A *p* value < 0.05 with two tails will be considered statistically significant.

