### Sequence generation and allocation concealment

Blocked randomization was conducted. A randomization sequence was generated using a computerized random number generator, and patients who met the enrolment criteria were randomized in a 1:1 ratio to either the control or esketamine anaesthesia group. Once the patient was qualified for the study, the project coordinator opened a sealed opaque envelope with random serial numbers. Only the statistician and the project coordinator knew the treatment allocation of each participant.

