### Sample size calculation

The sample size was calculated with PASS 15.0 (Number Cruncher Statistical Software, LLC, Kaysville, UT, USA). The hypothesis of this trial is that esketamine could be associated with fewer side effects of PONV than opioid anaesthesia. With *α* = 0.05 and a power of 90%, we assumed that esketamine anaesthesia may reduce the PONV rate from 37.3 to 20% according to a study by Ziemann-Gimmel et al. [25]; thus, a sample size of 139 for each group would be needed. According to previous studies, the general incidence of vomiting after surgical anaesthesia is approximately 30%, while the incidence of nausea is approximately 50% [26–28]. Therefore, proportions of 37.3% and 20% of PONV of patients in the F group and E group, respectively, were used to calculate the sample size.

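### PONV is tested without centre or procedure, and a logistic model is added to look for confounders; one prespecified adjusted analysis would be a cheap improvement

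*Protocol article*

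**What the plan says.** All references are to the protocol article.

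- **Primary outcome:** PONV incidence over 3 days, a binary outcome. Antiemetic dose and frequency are also recorded for analysis.
- **Statistical analysis:** "For categorical variables, cross-tabulation and the Pearson chi-squared test will be applied". No other test is named for PONV, and no term for centre or procedure appears. Then: "A logistic regression model will be applied to detect any potential confounding factors". The section lists no covariates and does not say how this model stands to the chi-squared test. The significance rule is a p "value < 0.05 with two tails will be considered statistically significant".
- **Study settings; Inclusion and exclusion criteria:** four participating centres; laparoscopic appendectomy or cholecystectomy.
- **Sequence generation and allocation concealment:** "Blocked randomization was conducted", with patients "randomized in a 1:1 ratio to either the control or esketamine anaesthesia group". Stratification is not mentioned.
- **Sample size calculation:** the treatment is assumed to "reduce the PONV rate from 37.3 to 20" per cent, and "a sample size of 139 for each group would be needed".
- **Secondary outcomes:** the recorded variables include anaesthesia and surgery time, intraoperative drugs, total propofol, episodes of low blood pressure and postoperative analgesics. All of these arise after randomisation.

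**The concern.** Three things stand out.

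1. Centre and type of operation are the obvious candidate predictors of PONV here. The Intervention section leaves supplementary dosing, reversal, the choice of analgesic and the choice of antiemetic to local judgement, so differences between centres are plausible. An analysis without these factors may give up some power.

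2. Detecting confounders is the wrong purpose for a regression in a randomised trial. The arms differ at baseline only by chance, and the test's 5% error rate already allows for that. Covariates belong in the model because they are expected beforehand to predict the outcome, not because the data show an imbalance.

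3. Nothing in the sentence keeps the search to baseline variables. The Discussion gives lower perioperative opioid consumption as a mechanism by which esketamine should reduce PONV. A screen that admitted drug consumption, low blood pressure or antiemetic use could adjust away part of the effect under test.

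**Working it through.** **Step 1. The plan's own figure.** Inputs from Sample size calculation and Statistical analysis: rates 0.373 and 0.20, two-sided alpha 0.05, power 0.90, 1:1 allocation. With unpooled variance:

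n = (1.960 + 1.282)² × [0.373 × 0.627 + 0.20 × 0.80] / (0.373 − 0.20)²
= 10.507 × (0.2339 + 0.1600) / 0.02993 = 138.3, rounded up to **139**.

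The stated figure is reproduced. The pooled-variance formula gives 142, and by that formula 139 per arm has 89.5% power. The sample size rests on the same unadjusted comparison that the Pearson test makes, so the two agree.

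**Step 2. What adjustment would do at the plan's rates.** Simulation with 278 patients and 4,000 runs per setting. Assumed, because the documents give no figures: four equal centres, a 50/50 procedure mix, unstratified blocks of 4 and four further weak covariates. The marginal rates were held at 37.3% and 20%. Strength is the SD of the centre effects on the log-odds scale and the procedure log odds ratio (OR).

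| Centre SD / procedure log OR | Power, Pearson | Power, logistic with centre and procedure | Change (points) |
|---|---|---|---|
| 0 / 0 | 0.896 | 0.892 | -0.4 |
| 0.3 / 0.3 | 0.900 | 0.894 | -0.6 |
| 0.5 / 0.7 | 0.896 | 0.910 | +1.4 |
| 0.8 / 1.0 | 0.896 | 0.925 | +2.9 |

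With no treatment effect, each of these two tests rejected in 0.047 to 0.054 of runs, so both hold their level.

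**Step 3. A second design.** Eight centre-by-procedure strata with normal effects, holding the conditional odds ratio at (0.20/0.80)/(0.373/0.627) = 0.42.

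| Stratum SD (log-odds) | Power, unadjusted | Power, stratified | Change (points) |
|---|---|---|---|
| 0 | 89.3% | 88.7% | -0.6 |
| 0.5 | 88.0% | 88.6% | +0.6 |
| 0.75 | 85.0% | 87.3% | +2.3 |
| 1.0 | 80.3% | 84.6% | +4.3 |

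Only the last column bears on the point. The fall down the unadjusted column is mostly a by-product of fixing the conditional odds ratio. At SD 1.0 the marginal rates become 39.4% and 23.9%, a difference of 15.5 points instead of 17.3. The ordinary two-proportion formula then gives 79.9% power at 139 per arm.

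**Step 4. If results could be chosen.** In the Step 2 simulation with no treatment effect, a third model used covariates screened at p < 0.10. The smallest p of the three analyses (Pearson, centre and procedure, screened) fell below 0.05 in 0.067 to 0.079 of runs, with a Monte Carlo standard error of about 0.004.

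**The case against.** The case for leaving the primary test alone is strong, and much of it stands. The Pearson test is valid, holds its level and matches the sample size basis. No stratified randomisation is stated that would oblige adjustment. The covariate list and the status of the logistic model are details that an article may leave to the full protocol or SAP, so their absence is not the point here. The word *blocked* is also a condensed description: it does not show that blocks were not formed within centres.

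A reader might infer that the trial will have two rival primary p-values, that covariates will be picked after the results are seen, or that the error rate is inflated. The text supports none of these. It assigns the chi-squared test to categorical variables, gives no timing for the regression, and does not say that the model supplies or replaces the primary result. The 0.07 to 0.08 in Step 4 shows what free choice would cost, not what is planned. Likewise, nothing ties the post-randomisation variables to the model; the wording merely fails to exclude them.

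A reader might also infer a clear loss of precision. That depends on prognostic strength, which is not given. Moreover, logistic adjustment does not shrink the standard error of the log odds ratio. The gain in power comes because the conditional odds ratio lies further from 1.

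What the objection does not remove is the stated aim of the regression. That is what the plan says, not a gap in it, and it is unsound under randomisation.

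**Conclusion.** The point holds as a recommended improvement. The primary test is not wrong and the sample size is not in question. The stated analysis leaves out two predictable sources of variation that the trial already records, and it gives the regression a purpose that does not suit a randomised comparison.

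The effect on power is small: about -1 point if centre and procedure do not predict PONV, and up to about +3 to +4 points if they predict it strongly. That range rests wholly on assumed prognostic strengths, equal centres or normal stratum effects and, in Step 2, an even procedure mix. The firmer reason for the change is clarity: one named analysis and baseline covariates fixed in advance leave no doubt about which result answers the primary question.

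**What to change.** Amend the Statistical analysis section, or the SAP, as follows:

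1. Name one primary analysis of PONV. Preferably this is a prespecified logistic regression on arm, centre and procedure, reported as a standardised risk difference with a 95% confidence interval. A Cochran-Mantel-Haenszel test stratified by centre and procedure is an acceptable alternative.
2. Keep the Pearson chi-squared test as a sensitivity analysis.
3. Replace the confounder-detection sentence with a short fixed list of baseline covariates. Age and ASA class could be added to centre and procedure if wanted.
4. State that variables arising after randomisation, such as surgery time, drug consumption, hypotension and rescue antiemetics, do not enter the model for the treatment effect.

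The cost is wording only, since centre and procedure are already known for every patient. The worst case is about one point of power if neither factor matters. The change should be dated before outcomes are examined by arm. The section is written in the future tense, so this is possible if analysis has not begun.

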### Inclusion and exclusion criteria

The inclusion criteria were as follows: (1) nonsmoking female patients who were 18–50 years old with a planned laparoscopic appendectomy or cholecystectomy from October 1, 2021, to October 1, 2022; (2) American Society of Anaesthesiologists (ASA) classification I–III; (3) no analgesic/sedative medication was used within 24 h before surgery; (4) no serious endocrine, cardiovascular and respiratory diseases before surgery; (5) no mental abnormality; and (6) provision of signed informed consent.

The exclusion criteria included patients who (1) had an allergic history of anaesthetic drugs or contraindications of esketamine, nonsteroidal anti-inflammatory drugs or dexmedetomidine; (2) had mental disorders, preoperatively screened using a neuropsychiatric inventory; (3) had poorly controlled or untreated hypertension with resting arterial pressure over 180/100 mmHg; (3) had addiction or dependence on opioid or hypnotic drugs; and (4) had respiratory infection or asthma before surgery.

Patients who were enrolled but met one of the following criteria were excluded from the study: (1) incomplete case report form or lost to follow-up and failed to make an effective and safety assessment, (2) change of anaesthesia method due to unexpected incident or surgery requirement during the surgery, (3) operation could not be continued due to unexpected incident during the surgery and (4) other diseases post-surgery required urgent treatment.

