### Secondary outcomes

Variables indicating recovery status included the time to spontaneous respiration, awakening, eye opening and extubation after stopping anaesthetic agents. The scales used for patient pain, sedation level and overall recovery assessment included the visual analogue score (VAS), Modified Observer’s Assessment of Alertness/Sedation (MOAA/S), Bruggrmann Comfort Scale (BCS) [20] and 15-item Quality of Recovery Questionnaire (QoR-15) [21]. Delirium and cognition were assessed with the Confusion Assessment Method and Mini-Mental State Examination [22, 23]. Anxiety and depression were evaluated with the Hospital Anxiety and Depression Scale [24]. All scales were assessed at 0, 2, 4, 8, 24 and 72 h after waking. The total amount of propofol consumption, all drugs used during anaesthesia and analgesics for postoperative pain management were recorded. Side effects or adverse events were recorded for 3 postoperative days, and thereafter, the hospital stay time was recorded. The intraoperative variables collected included anaesthesia and surgery time, intraoperative medication, blood loss, fluid and blood transfusion, urine output, mean arterial pressure (MAP) and heart rate, time and duration of low blood pressure (MAP < 60 mmHg) and nociceptive level of SPI. The average percent change to baseline in mean arterial pressure and heart rate was also calculated. Percent change for arterial pressure = (MBPT1−*x* − MBPT0)/MBPT0 × 100; percent change for HR = (HRT1−*x* − HRT0)/HRT0 × 100. The recorded time points are as follows: after entering the operation room, patients were allowed to be quiet for 10 min, and blood pressure and heart rate were measured twice (15 min apart) and the average values were recorded as the basic blood pressure and heart rate (T0), when TCI propofol reached equilibrium (T1), 3 min after sufentanil or esketamine infusion (T2), immediately after intubation (T3), 5 min after intubation (T4), time to pneumoperitoneum (T5) and then every 15 min (T6−*x*) until the end of the surgery.

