According to a recent study on Chinese patients, the administration of esketamine as a relatively small dose was generally safe for anaesthesia without consideration of sex differences [32]. In fact, several advantages of esketamine in clinical anaesthesia have recently been proven. First, it creates less impairment on patients’ spontaneous breathing and airway reflexes as well as circulation stability due to an increase in sympathetic tone. In addition, Eberl et al. [17] reported that low-dose esketamine reduces the total amount of propofol necessary for sedation during ERCP while proving satisfactory sedative effects. Furthermore, many studies report that a combination of propofol with ketamine may result in a better quality of sedation and analgesia, with shorter recovery time, better satisfaction of patients and fewer respiratory or cardiovascular side effects [33]. Despite all these benefits, one widespread concern of esketamine is that it can produce psychotomimetic effects that may be associated with cognitive impairment [13].

In this trial, we hypothesized that OFA with esketamine could reduce the PONV rate after laparoscopic surgery based on several possible underlying mechanisms. On the one hand, it certainly reduced the consumption of opioids perioperatively, which has been proven to be one of the main risk factors for PONV [34]. On the other hand, esketamine is also known for its effective effects in maintaining spontaneous breathing and airway reflexes during anaesthesia; in addition, it can increase sympathetic tone and result in less hypotension and cardiac depression [35]. The reduced interference of esketamine on respiratory and circulatory systems during surgery also provides better conditions for ERAS in patients.

However, research on the advantages or disadvantages of esketamine in surgical anaesthesia remains deficient, and further randomized trials with larger sample sizes are urgently needed in this area. In this study, we also plan to investigate intraoperative circulatory stability as well as other recovery indices for esketamine in anaesthesia for laparoscopic appendectomy and cholecystectomy.

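### As written, the AUC for heart rate and blood pressure mixes average level with length of surgery; a time-weighted average would avoid this and keep power

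*Protocol article*

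**What the plan says.** The Statistical analysis section of the protocol article names one summary for comparing heart rate and non-invasive blood pressure between groups: "the area under the curve (AUC) for each value will be calculated over the different measurement time points during the procedure". The sentence is printed twice. It mentions no division by observed time, baseline subtraction, common window or adjustment for duration.

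The Secondary outcomes section sets the time points. After a baseline (T0) averaged from two readings, there are points tied to induction and intubation, then "time to pneumoperitoneum (T5) and then every 15 min", continuing "until the end of the surgery". Both the number of readings and the time they span therefore depend on the patient.

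The inclusion criteria pool two operations ("planned laparoscopic appendectomy or cholecystectomy"). Duration is recorded ("The intraoperative variables collected included anaesthesia and surgery time"), but the analysis text does not link it to the AUC.

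Two other haemodynamic summaries are planned in Secondary outcomes. One is percent change ("The average percent change to baseline in mean arterial pressure and heart rate was also calculated"); the other is the time and duration of MAP below 60 mmHg. The Discussion states the interest: "we also plan to investigate intraoperative circulatory stability".

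**The concern.** An area under a curve of pressure against time has units of mmHg × min. If the window is the whole operation and the area is not divided by its length, a longer operation gives a larger value at the same pressure. With MAP steady at 85 mmHg, 45 min gives 85 × 45 = 3825 mmHg·min and 60 min gives 85 × 60 = 5100 mmHg·min.

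Two things could follow. Variation in operating time, which says nothing about circulation, adds noise and can hide a real difference between esketamine and sufentanil. And if operating time differed between the arms, that difference would be read as a haemodynamic one. At stake is the secondary question of circulatory stability, which bears on the rationale for esketamine; the PONV comparison is not involved.

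**Working it through.** **The plan's own figure.** The article gives no figure for the AUC comparison. Its only computed figure is 139 per group for PONV (37.3% against 20%, two-sided α 0.05, power 90%). It reproduces with the unpooled normal approximation: (1.960 + 1.282)² × (0.373 × 0.627 + 0.2 × 0.8) / 0.173² = 138.3, rounded up to 139. This matters here only because it fixes the number per arm.

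**Inputs.** From the documents: 139 per arm, 1:1 allocation, two-sided 0.05, a patient-specific window. Assumed, because the documents do not give them: mean MAP 85 mmHg with between-patient SD 10, mean duration 60 min with SD 10, 20 or 30, and level independent of duration.

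**Variance of the undivided AUC.** Write AUC = M × T, with M the patient's mean level and T the duration. For independent M and T:

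Var(AUC) = (mean M × SD T)² + (mean T × SD M)² + (SD M × SD T)²

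At duration SD 20: (85 × 20)² + (60 × 10)² + (10 × 20)² = 2,890,000 + 360,000 + 40,000 = 3,290,000, so the SD is about 1814 mmHg·min. The share due to duration is 2,890,000 / 3,290,000 = 88%.

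| Duration SD (min) | SD of AUC (mmHg·min) | Share due to duration |
|---|---|---|
| 5 | 737 | 33% |
| 10 | 1045 | 66% |
| 20 | 1814 | 88% |
| 30 | 2637 | 94% |

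**Power for a true 5 mmHg difference, equal durations.** The AUC difference is 5 × 60 = 300 mmHg·min. At duration SD 20 the standardised difference is 300 / 1814 = 0.165. Multiplied by √(139/2) = 8.34 this gives a noncentrality of 1.38 and power of about 28%. For the time-weighted mean it is 5 / 10 = 0.5, noncentrality 4.17, power about 99%.

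**Simulation** (3000 replicates per scenario, gamma-distributed durations, two-sample t test):

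| Scenario | Summary | SD 10 | SD 20 | SD 30 |
|---|---|---|---|---|
| No difference in pressure or duration | Undivided AUC | 4.9% | 5.4% | 4.8% |
| | Time-weighted mean | 4.6% | 5.7% | 5.1% |
| 5 mmHg difference, equal durations | Undivided AUC | 64% | 27% | 17% |
| | Time-weighted mean | 99% | 99% | 99% |
| Identical pressures, means 5 min apart | Undivided AUC | 92% | 50% | 25% |
| | Time-weighted mean | 5% | 6% | 5% |

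The closed form agrees with the simulation to within about 3 percentage points. At a duration SD of only 5 min it gives about 92% power for the undivided AUC (300 / 737 = 0.407; × 8.34 = 3.39), so the loss is small if operations are very uniform in length.

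**Cancellation.** If the arm with 5 mmHg higher pressure also finishes 3.5 min sooner, the expected AUCs are 90 × 56.5 = 5085 and 85 × 60 = 5100. The undivided AUC then rejects in about 5% of trials; the time-weighted mean still rejects in about 99%.

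**The case against.** The strongest reply has four parts.

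- **The article never says the AUC is undivided.** It is silent, and a full protocol or analysis plan may normalise it. This stands as a caution. But the article does name the summary and its time points and lets them run to the end of surgery; followed as it reads, the result scales with operating time.
- **The size depends on an unknown duration spread.** This stands. The duration share runs from 33% to 94% over the SDs tried. A reader might infer that the AUC measures length of surgery rather than circulation; the documents do not support that, because the AUC reflects both in a proportion they do not fix.
- **Allocation is randomised.** This stands too. A reader might infer that false positives are the main danger, but without a treatment effect on duration the rejection rate under no difference stays near 5%. The 92%, 50% and 25% figures need a real difference in mean duration, and the article gives no reason to expect one. The main harm is lost power.
- **Other measures are planned, and the endpoint is not primary.** Average percent change does not grow with length of surgery, and time below 60 mmHg describes hypotension directly. Circulatory stability therefore does not rest on the AUC alone. Even so, the AUC is the summary that the Statistical analysis section names for the between-group comparison.

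Restricting the main comparison to a common window from T1 to pneumoperitoneum (T5) would not be a good answer. T1 precedes the study drug, T5 is an event reached at a variable time, and every later reading would be lost, including those after any repeat doses.

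**Conclusion.** The concern holds in a limited form. As written, the AUC mixes average level with length of surgery. With no difference in duration between arms, the test remains valid but loses power: about 64%, 27% and 17% for a true 5 mmHg difference at duration SDs of 10, 20 and 30 min, against about 99% for a time-weighted mean. Only if mean duration differs between arms does it also produce false haemodynamic differences.

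These figures rest on the assumed pressure and duration distributions and on independence of level and duration. They show the likely order of the effect and do not predict this trial's result. The change is worth making for the secondary haemodynamic comparison; it does not touch the PONV result or the sample size.

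**What to change.** In the Statistical analysis section, replace the AUC sentence (and delete its repeat) with:

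- **Summary:** the time-weighted average of MAP and of heart rate, that is, each patient's AUC divided by that patient's own observed time, over all readings after the study drug, from T2 to the end of surgery. T2 follows the numbering in Secondary outcomes (3 min after the study-drug infusion); the Fig. 1 legend labels the same point t3, so the text should say which numbering applies.
- **Comparison:** between arms by a linear model with the T0 value as covariate.
- **Supportive:** keep the planned percent change and the time and duration of MAP below 60 mmHg as descriptions of stability. A time-weighted average measures level, not variability, so these still have a role.

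The cost is a change of wording and a little extra analysis work. All the readings, their times and the baseline are already in the data-collection plan, so no new data are needed.

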**Methods/design:**

The study was designed as a prospective, randomized, controlled, multicentre trial. A total of 278 patients were enrolled; participants were nonsmoking female patients aged 18–50 years and scheduled for laparoscopic appendectomy or cholecystectomy, ASA at I–III, with no serious physical or mental diseases. Both groups received usual perioperative care except for the analgesic medication of either esketamine or sufentanil. The primary outcome was the incidence of PONV 3 days after surgery. Secondary outcomes included recovery status, pain, sedation level and overall recovery, delirium and cognition, anxiety and depression and total consumption of analgesic agents.

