**Fig. 1 Fig1:**
[figure not shown]
Schedule of enrolment, intervention and assessment according to the Standard Protocol Items: Recommendations for Interventional Trials (SPIRIT) statement. Time points for implement of the study: *t*_−1_: when enrolled, *t*_0_: allocation, *t*_1_: before anaesthesia, *t*_2_: TCI propofol reached equilibrium, *t*_3_: in 3 min after sufentanil or esketamine infusion, *t*_4_: immediately after intubation, *t*_5_: in 5 min after intubation, *t*_6_: pneumoperitoneum, *t*_7−*x*_ in each 15 min till the end of the surgery; *t*_*a*−*g*_ refers to 0, 2, 4, 8, 24, 48 and 72 h after anaesthesia

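### The AUC for heart rate and blood pressure runs to the end of each patient's own operation without time standardisation, so it mixes operation length with haemodynamic level and loses power

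*Protocol article*

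**What the plan says.** The Statistical analysis section gives the summary measure for comparing HR and NIBP between groups: "the area under the curve (AUC) for each value will be calculated over the different measurement time points during the procedure". The sentence is printed twice. For continuous variables in general the same section says "continuous variables will be analysed using the independent Student’s" t test, with Mann-Whitney U for non-normal data.

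The Secondary outcomes section defines the measurement points. After a baseline and several event-linked readings they continue as "time to pneumoperitoneum (T5) and then every 15 min", and they run "until the end of the surgery". The legend of Fig. 1 gives the same variable end: "in each 15 min till the end of the surgery".

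Three other statements bear on the point:

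- The Abstract describes patients "scheduled for laparoscopic appendectomy or cholecystectomy", so two different operations share one analysis.
- Secondary outcomes says "The intraoperative variables collected included anaesthesia and surgery time", so operation length is recorded.
- Secondary outcomes also says "The average percent change to baseline in mean arterial pressure and heart rate was also calculated", and gives formulas for it.

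Nowhere does the article divide the AUC by elapsed time, fix a window common to all patients, subtract a baseline from the AUC or adjust the comparison for duration.

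**The concern.** HR and arterial pressure stay far above zero throughout an operation. The area under such a curve is close to its mean level multiplied by the length of the window. When each patient's window ends with her own surgery, a longer operation gives a larger AUC at the same heart rate or pressure. The unit (mmHg·min or beats) then cannot be read as high or low pressure or heart rate.

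The Discussion names intraoperative circulatory stability as something the trial will investigate. On that question a real difference in level could go undetected, because variation in operating time enters the AUC as noise. If operating time truly differed by arm, that difference could also be reported as a haemodynamic effect.

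**Working it through.** **Inputs from the protocol article.** 139 patients per group (Sample size calculation); two-sided 5% level and unadjusted tests (Statistical analysis); window ending with each patient's surgery (Secondary outcomes, Fig. 1 legend). The article states no design figure for the AUC comparison, so there is none to reproduce.

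**Inputs assumed.** The article gives no mean or SD for operating time, HR or pressure. I assume mean HR 72 bpm with between-patient SD 10, a mean window of 60 min with SD 10, 20 or 30 min, duration independent of level, and a true difference of 5 bpm.

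**Step 1: can the ordering reverse?** AUC ≈ L × T, where L is the patient's mean level and T her window length.

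- 80 mmHg × 90 min = 7200 mmHg·min
- 90 mmHg × 60 min = 5400 mmHg·min

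The patient with the lower pressure has the larger AUC. This step needs no assumption about spreads.

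**Step 2: power of the time average.** SE = 10 × √(2/139) = 10 × 0.120 = 1.20 bpm. Ratio 5/1.20 = 4.17. Power = Φ(4.17 − 1.96) ≈ 0.99.

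**Step 3: power of the undivided AUC.** For independent L and T,

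Var(LT) = μ_T²σ_L² + μ_L²σ_T² + σ_L²σ_T².

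The difference in mean AUC is 5 × 60 = 300. The first term is always 3600 × 100 = 360,000.

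| SD of T (min) | Var(LT) | SD | SE | 300/SE | Power |
|---|---|---|---|---|---|
| 10 | 360,000 + 518,400 + 10,000 = 888,400 | 942.5 | 113.1 | 2.65 | 0.76 |
| 20 | 360,000 + 2,073,600 + 40,000 = 2,473,600 | 1572.8 | 188.7 | 1.59 | 0.36 |
| 30 | 360,000 + 4,665,600 + 90,000 = 5,115,600 | 2261.8 | 271.3 | 1.11 | 0.20 |

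A simulation of 4000 trials per scenario with gamma-distributed durations gave 72%, 33% and 18%. Rounded, the two approaches give about 75%, 35% and 20%.

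**Step 4: a second set of assumptions.** Mean arterial pressure 85 mmHg, mean duration 60 min, log-normal durations, true difference 5 mmHg, 139 per arm. The time average has power of about 1.00 when the coefficient of variation (CV) of the level is 10%, and 0.90 when it is 15%.

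| CV of duration | AUC power, level CV 10% / 15% | Share of AUC variance due to duration, level CV 10% / 15% |
|---|---|---|
| 10% | 0.93 / 0.78 | 50% / 31% |
| 20% | 0.59 / 0.49 | 79% / 63% |
| 30% | 0.34 / 0.31 | 89% / 79% |
| 40% | 0.22 / 0.21 | 93% / 86% |

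Power is lost in every row. Duration accounts for more of the variance than level only where its CV exceeds that of the level.

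**Step 5: what would a real difference in duration do?** With identical HR but operations truly 5 min longer on average in one arm, the AUC difference is 72 × 5 = 360. Dividing by the SEs in step 3 gives 3.18, 1.91 and 1.33, so the AUC test rejects in about 89%, 48% and 26% of trials. The time average rejects in 5%. These figures apply only if such a systematic difference exists.

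**The case against.** **No standardisation is mentioned, but that is only silence.** A journal article condenses the full protocol, and a separate analysis plan might divide by time or restrict the window. This stands in part, and the reading here is of the article as written. However, the article names both the summary measure and the points over which it runs, and on a plain reading that combination is a poor choice rather than an omitted detail.

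**Circulatory stability does not rest on the AUC alone.** This stands. The average percent change from baseline in mean arterial pressure and HR does not grow with duration, and the general tests for continuous variables would apply to it. The duration of low blood pressure is also recorded. The AUC is nevertheless the measure that the Statistical analysis section names for comparing HR and NIBP.

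**A reader might infer that the AUC measures operation length more than haemodynamic level.** The documents do not support this, because it depends on spreads they do not give. In step 4 it is a tie at equal CVs of 10%, and false at a duration CV of 10% with a level CV of 15%. Two operations make a wide spread plausible but do not establish it.

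**A reader might also infer that chance imbalance in operating time produces false positives.** It does not raise the error rate. Under 1:1 randomisation, chance imbalance is already within the 5%. The rejection rates in step 5 need a true difference in operating time between arms, and the article gives no reason to expect one.

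**The window may include time before surgery.** The article does not fix where the AUC starts. If it starts at baseline, doubling the surgery does not double the AUC, and the CV of the window is smaller than that of surgery alone. This moves the case toward the upper rows of step 4; it reduces the loss but does not remove it.

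**Conclusion.** The concern holds in limited form. As written, the AUC mixes operation length with haemodynamic level, and patients can be ranked in the wrong order. If duration does not depend on arm, the test keeps its 5% level, and the harm is lost power and a result that is hard to interpret. Under the HR assumptions, power falls from about 99% to about 75%, 35% and 20% at a duration SD of 10, 20 and 30 min. The size rests on assumed means and spreads; the direction does not. A spurious group difference arises only if operating time truly differs by arm.

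This is a secondary measure. The PONV primary outcome and the 139 per group are untouched. The change should be made because it is nearly free, not because the trial's main conclusion is at risk.

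**What to change.** In the Statistical analysis section, replace the AUC by the time-weighted average: the trapezoidal AUC on actual clock times, divided by the elapsed time from first to last reading. Alternatively, compute the AUC over one fixed window that all patients complete. State the starting point, apply the same rule to HR and to each NIBP component, and delete the duplicated sentence.

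The cost is one sentence. The readings are already scheduled at defined times and surgery time is already collected, so no new data, patients or changes to care are needed.
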